## 2. Background

COVID-19 vaccines are being rolled out in many countries all over the world. Promising efficacy data from phase three vaccination trials are being confirmed with real-world data from countries like Israel and the United Kingdom where large proportions of the population have already been vaccinated (1–3).

Vaccine supply has proven an important limiting factor for the speed of vaccination campaigns. Indeed, vaccine demand largely surpasses production capacity of the different manufacturers. In order to cope with this scarcity, different strategies have been proposed and implemented, including a delayed second dose and a single instead of dual dose for previously infected people. Another possible strategy is a reduction of the vaccine dose for those population groups who generally have better immunologic vaccine responses, which is the subject of this clinical trial (4). Indeed, in this study we will investigate immune responses to a reduced dose of the BNT162b2 mRNA vaccine of BioNTech/Pfizer.

Data from a dose-escalating phase 1 trial in healthy adults 18 to 85 years of age comparing two doses of 10µg, 20µg, 30µg and 100µg indicated that a dose of 30µg of BNT162b2 achieved the best immune response in participants of all ages (5). As a result, a phase2/3 trial was conducted and the vaccine was finally marketed at a dosage of 30µg (6). These immune responses were age dependent, however. While people aged 65-85 years (N=24) had markedly better responses with 30µg as compared to 20µg, this was not the case for people aged 18-55 years (N=24). Indeed, SARS-CoV-2 specific binding and neutralizing antibody titers were even slightly higher in the 20µg group as compared to the 30µg group. We therefore propose to conduct a clinical trial investigating immune responses comparing a 20µg versus 30µg dose of BNT162b2 in a larger cohort of 150 subjects..

## 3. Objectives and outcomes

We aim to include 150 adults aged 18-55 years from five Mensura EDPB sites. These will be equally randomized in two study arms receiving two doses of:

- Arm 1: 20µg BNT162b2
- Arm 2: 30µg BNT162b2

We aim to include up to 25 previously SARS-CoV-2 infected subjects per arm. The objectives of this study include assessing the immunogenicity (both humoral and cellular), safety and reactogenicity of a reduced vaccine dose.

### 3.1. PRIMARY OBJECTIVE AND OUTCOME

- The primary objective is to prove non-inferiority of immunogenicity of a reduced BNT162b2 vaccine dose (20µg) versus the reference vaccine dose (30µg).
- The primary outcome is the geometric mean titer (GMT) of binding (IgG) antibodies specific to the receptor binding domain (RBD) of SARS-CoV-2 at four weeks after the second dose.

Data from the literature and from our own PICOV-VAC data indicate strong correlation between titers of RBD binding antibodies and neutralizing antibodies. As methods to measure RBD binding antibodies can be implemented more rapidly than neutralizing antibody assays, we consider that RBD binding antibodies are a good surrogate for neutralizing antibodies and can therefore be used as a primary endpoint for this study.

### 3.2. SECONDARY OBJECTIVES AND OUTCOMES

- GMT of RBD-specific binding antibodies at the time of the second dose, six months and one year after the first dose.
- GMT of neutralizing antibody titers against wild type and variant SARS-CoV-2 viruses at four weeks after second dose administration.
- Cellular immunity parameters (i.e. Memory B-cell responses, T-cell responses, etc) at all clinically and biologically relevant time points.
- Safety and reactogenicity of the different vaccine regimens as defined by the severity, duration and amount of adverse events experienced after each vaccine dose.

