### **Sampling visits**

An overview of the different sample types and volumes at each study visit is summarized in table 1. Venous blood will be collected on the day of the first and second dose as well as four weeks after the second dose, and six months and one year after the first dose. Five mL of blood will be collected from all study participants at all study visits. From a random selection of 20 participants per study arm (40 in total), 36mL of heparinized blood will be collected on the day of the first dose as well as four weeks after the second dose and six months after the first dose.

The sampling activity (date, sample types collected) is documented in the eCRF. Samples are handled as detailed in the sampling manual.

One week after each vaccination dose, participants will be invited by email and text message by the research nurse to fill in a questionnaire collecting information on the reactogenicity of the vaccine.

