## Analysis

### Data analysis

Analysis of all data collected within this study will be performed by Sciensano. Questionnaire responses will always be coded. All analyses will be performed in R (R Core Team (2018), available from <https://www.R-project.org/>), STATA or SAS.

Meaningful laboratory results of each participant will be communicated to the research nurse who will be able to communicate them to the participants. This includes the anti-SARS-CoV-2 antibody status at the primary endpoint and at the end of the study.

As already mentioned, these tests are for research and not diagnostic purposes, and depending on lab capacity, there will be a delay in the communication of the results. The global results of the study will be communicated to each participating center at the end of the study in the form of a report and/or presentations.

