### Statistical analyses

The analysis described here will be coordinated by the Sponsor. Any later analyses on the linked data will also be conducted by the Sponsor.

All of the participants who meet the eligibility criteria will be included in the main analysis. Descriptive analyses will be used to report participant characteristics. The level of antibody titers in each of the study arms will be analyzed with the Kruskal-Wallis test, while participant demographics (e.g. age, gender) will be taken into account (confounders). Furthermore, risk factors and correlations with antibody detectability will be evaluated. P-values below 0.05 will be considered statistically significant.

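### The only test named for antibody titres, an arm-wise Kruskal-Wallis, suits the repeated RBD GMT outcomes poorly; any bias in late comparisons is modest and arises only if titre-related loss differs between arms

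*Protocol*

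**What the plan says.** Protocol section 3.2 sets as a secondary outcome the "GMT of RBD-specific binding antibodies at the time of the second dose, six months and one year after the first dose". The four-week titre is the primary outcome (section 3.1: "specific to the receptor binding domain (RBD) of SARS-CoV-2 at four weeks after the second dose") and is not part of this list.

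The measurements are repeated on the same people. Under Sampling visits, "Five mL of blood will be collected from all study participants at all study visits", and Table 1 shows five visits.

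Under Statistical analyses, "The level of antibody titers in each of the study arms will be analyzed with the Kruskal-Wallis test", and the sentence goes on: "while participant demographics (e.g. age, gender) will be taken into account (confounders". The test is tied to no particular visit. On the analysis set the section says "All of the participants who meet the eligibility criteria will be included in the main analysis", and on significance "P-values below 0.05 will be considered statistically significant". It names no GMT ratio, interval or longitudinal model for titres.

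Four other places bear on loss before the late visits:
- Discontinuation criteria: anyone may leave, and participants who do not supply questionnaire information are discontinued.
- Data analysis: laboratory results can be passed on to participants. "This includes the anti-SARS-CoV-2 antibody status at the primary endpoint and at the end of the study".
- Baseline activities: data collected before withdrawal of consent are kept.
- Discontinuation criteria and Blinding/unblinding: if 20 µg proves inferior at the primary time point, participants are unblinded and a third dose is offered.

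**The concern.** The protocol has chosen a method for titres, and that method does not fit the outcomes it defines.

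- **No estimate.** The outcomes are GMTs, for which the natural summary is a ratio with a confidence interval. With two arms, Kruskal-Wallis is a rank-sum test and returns a p-value.
- **No adjustment.** The test takes no covariates, so it cannot do what the rest of its own sentence promises for age and gender.
- **One value per person.** It can only be run visit by visit. A rank test at one year ranks one-year titres, so a participant with a four-week titre and no one-year sample contributes nothing, although the earlier titre is on file.

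The last feature matters if leaving depends on the four-week titre and more such people leave one arm than the other. If 20 µg gives truly lower titres, a single rule for leaving removes more 20 µg participants. Those who remain then look somewhat closer to the 30 µg arm at six months and one year. The titre at dose 2 precedes any four-week result, so this route cannot affect it.

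**Working it through.** The protocol gives no attrition rate, within-person correlation or late standard deviation, and no figure for the late comparisons. There is no stated result to reproduce, so the size rests on assumptions.

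**Inputs from the protocol.** 150 participants in two equal arms, so 75 per arm; SD 0.27 log10 at four weeks; margin 0.15 log10; planning assumption of a true difference of 0.

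**Assumptions.** True difference -0.15 log10 at four weeks and one year; SD 0.30 at one year; within-person correlation ρ of 0.5 to 0.8; leaving depends only on the four-week titre. Two loss patterns, each about 20% overall:
- A: 60% of the lowest quarter and 7% of the rest (0.25 × 0.60 + 0.75 × 0.07 = 0.2025).
- B: 40% and 13% (0.25 × 0.40 + 0.75 × 0.13 = 0.1975).

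**Step 1: who falls in the lowest quarter.** Set the 30 µg mean to 0. The pooled lower-quartile cut is then -0.264. For 20 µg, z = (-0.264 + 0.15)/0.27 = -0.423, so 33.6% lie below it. For 30 µg, z = -0.264/0.27 = -0.979, so 16.4% do. The normal densities φ(z) are 0.365 and 0.247.

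**Step 2: loss by arm.** Pattern A: 24.8% in 20 µg and 15.7% in 30 µg. Pattern B: 22.1% and 17.4%.

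**Step 3: shift in the four-week mean of those remaining.** Shift = 0.27 × φ(z) × (loss below the cut - loss above it)/(fraction kept).
- A, 20 µg: 0.27 × 0.365 × 0.53/0.752 = 0.0694. A, 30 µg: 0.27 × 0.247 × 0.53/0.843 = 0.0419. Difference 0.0275.
- B, 20 µg: 0.27 × 0.365 × 0.27/0.779 = 0.0341. B, 30 µg: 0.27 × 0.247 × 0.27/0.826 = 0.0218. Difference 0.0123.

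**Step 4: carry over to one year.** Multiply by ρ × 0.30/0.27.

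| Pattern | Shift, ρ = 0.5 | Shift, ρ = 0.8 | Apparent difference |
|---|---|---|---|
| A | 0.015 | 0.024 | -0.135 to -0.126 |
| B | 0.007 | 0.011 | -0.143 to -0.139 |

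A simulation of 3,000 trials per scenario agrees: -0.134 to -0.126 for A and -0.143 to -0.140 for B. A likelihood estimate that also uses the four-week titre gives -0.149 to -0.151. On the ratio scale the truth is 10^-0.15 = 0.708 and the apparent value lies between 10^-0.143 = 0.719 and 10^-0.126 = 0.748, which is 2 to 6% higher.

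**Step 5: equal loss.** With no true difference, both arms have 25% below the cut (z = -0.674, φ = 0.318). Under A each arm's four-week mean moves by 0.27 × 0.318 × 0.53/0.7975 = 0.057, and under B by 0.27 × 0.318 × 0.27/0.8025 = 0.029. Each arm's own one-year mean is then too high by 0.016 to 0.051 log10, but the two shifts cancel and the arm difference is unbiased. Simulations with equal titre-dependent loss of 10% or 20% agree (difference within about 0.002 log10), and Kruskal-Wallis then rejects a true null 4 to 6% of the time.

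**Step 6: other unequal-loss rules.** These use SD 0.27 at both visits, ρ of 0.5 or 0.8, and log-odds of leaving that rise by 1 or 2 per SD of lower titre.
- One common rule, true difference -0.15, 10% or 20% lost from 30 µg and therefore 15 to 34% from 20 µg: shift +0.006 to +0.032. Power falls from 82-88% to 69-84%, partly because fewer people remain.
- 20% against 10% lost: shift +0.010 to +0.027.
- 30% against 10% lost: shift +0.022 to +0.051. Nothing in the protocol points to so wide a split.

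**Step 7: precision.** With purely random 20% loss, the standard error of the one-year difference goes from 0.0560 to 0.0549 (ρ = 0.5) or from 0.0541 to 0.0506 (ρ = 0.8), a gain of 2 to 6%.

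**The case against.** The strongest reply is that much of this reads silence as a defect. The protocol does not say that late analyses are confined to those still sampled. Longitudinal models and missing-data rules for secondary outcomes are commonly left to an SAP, which is not shown. That stands for missing-data handling, which is not the finding. It does not cover the test itself, which the protocol states and which cannot deliver a GMT ratio or the promised adjustment.

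A reader might infer that late comparisons are biased whenever low responders leave. The documents do not support that. Equal loss leaves the arm difference essentially unbiased, and the planning assumption is a true difference of 0. Discontinuation is tied to questionnaires or the participant's own choice, not to titre. Two provisions limit loss: participants should remain employees until study end (Inclusion criteria), and a questionnaire not yet filled in at sampling is completed with the nurse (Data flow and management). Nothing links being told one's antibody status to leaving.

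The scenario that produces bias also disturbs the late visits by another route. With a true -0.15, the four-week standard error is 0.27 × √(2/75) = 0.044 and z is about 3.4, so a two-sided 95% interval would exclude zero in about 93% of trials. If that counted as inferiority, the third-dose offer would follow and late 20 µg titres would change. A mixed model does not solve this by itself. The objection stands and shapes the fix.

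A reader might also credit the model with cutting the standard error of the arm difference in change from 0.062 to 0.028-0.044. The larger figure treats visits as independent, which the protocol never proposes, and change is not a listed outcome.

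**Conclusion.** The point holds in a limited form. The named test fits the secondary RBD outcomes poorly: it gives no ratio or interval, makes no adjustment for age and gender, and leaves earlier titres unused. This follows from the text and needs no assumption about loss.

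Bias is a conditional addition. It requires titre-related loss that differs between arms. At about 20% assumed loss and an assumed true difference of -0.15, it is roughly 0.01 to 0.02 log10 (0.007 to 0.024 across the cases worked), under half the standard error of about 0.055. The inference that the plan will make the reduced dose look more durable than it is goes beyond the documents, because the attrition rate, the loss pattern and the true difference are all assumed. This is a minor point on secondary outcomes only.

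**What to change.** For the secondary RBD outcomes, name a repeated-measures mixed model on log10 titre as the main analysis:
- arm, visit, arm-by-visit, age, gender and baseline infection status (or baseline titre) as terms, with unstructured within-person covariance. Infection status belongs there because up to 25 of the 75 per arm may be previously infected (section 3);
- the 20/30 µg GMT ratio with confidence interval reported at each visit;
- Kruskal-Wallis kept as a sensitivity analysis.

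State in advance how titres taken after any third dose offered under Discontinuation criteria and Blinding/unblinding enter this analysis, so that titres from before and after such a dose are not pooled without a rule.

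The cost is a change of analysis wording and a few lines of code in the software already named, with no new data or participants. The small downside is that the model relies on approximate log-normality and on loss being explained by observed data.

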#### Discontinuation criteria

All participants retain the right to end their participation in the study at any point in time. Participants who fail to provide the necessary information through the questionnaires, will be discontinued from the study, since any correlation analysis with biological measurements becomes impossible.

The primary objective of the study is to prove non-inferiority of anti-RBD binding antibody titers four weeks after the second dose of the 20µg versus 30µg study arm. If the primary outcome of the study reveals an inferiority of the 20µg dose, participants in the 20µg dose arm will be offered a third, 30µg dose of the study vaccine.

Although no correlate of protective immunity has been validated yet, a relationship between vaccine-induced SARS-CoV-2 antibodies and protection has been proposed (7).

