## Blinding/unblinding

Everyone involved in the study will be blinded to the study arm allocation of each participant, except for the study nurses administering the vaccine.

When the primary outcome of the study has been reached (28 days after the second dose), an interim analysis will be conducted to determine whether the reduced vaccine dose induces an inferior immune response as compared to the regular dose or not. In case of non-inferiority, there will be no need for unblinding before the end of the trial. In case of inferiority, study participants will be unblinded, informed about which study arm they were allocated to and offered a third dose (of 30µg) of BNT162b2.

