### **Vaccination**

Depending on the randomization, participants will either receive two doses of 20µg or two doses of 30µg of the BioNTech/Pfizer SARS-CoV-2 mRNA vaccine, with a three week interval between both doses.

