### 7.2. BENEFITS

In general, the study will provide insight in the possibility of reducing the vaccine dosage required to achieve acceptable immune responses. This might help alleviate the current vaccine scarcity and speed up vaccination campaigns.

In particular, study participants will have the possibility to be vaccinated significantly earlier than foreseen by the Belgian national vaccination campaign, since they all belong to low priority groups. Secondly, those participants receiving a lower dose of the vaccine are expected to experience fewer and less severe side effects than they would with a full dose vaccination (5,9). Finally, if immune responses in the lower dose arm turn out to be inferior to the regular dose arm, these participants will be offered a third, regular dose to boost their immunity.

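### If the 28-day result is judged inferior, the third dose offered to the 20 µg arm means the 1-year, and probably the 6-month, antibody comparison no longer describes the two-dose regimens

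*Protocol*

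**What the plan says.** Section 3 defines the two arms as two doses of 20 µg and two doses of 30 µg. Section 3.2 lists as a secondary outcome "GMT of RBD-specific binding antibodies at the time of the second dose, six months and one year after the first dose". Cellular parameters are a further secondary outcome.

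The third dose appears in three places. Discontinuation criteria: if the primary outcome shows inferiority, "participants in the 20µg dose arm will be offered a third, 30µg dose of the study vaccine". Blinding/unblinding: "When the primary outcome of the study has been reached (28 days after the second dose), an interim analysis will be conducted", and then "In case of inferiority, study participants will be unblinded, informed about which study arm they were allocated to and offered a third dose". Section 7.2, on the lower-dose arm: "these participants will be offered a third, regular dose to boost their immunity". The blinding section does not itself repeat the restriction to the 20 µg arm; the other two sections do, and that reading is taken here.

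The sampling plan has no matching branch. Sampling visits places blood draws on the days of dose 1 and dose 2 and at "four weeks after the second dose, and six months and one year after the first dose", and Table 1 shows the same visits. Statistical analyses says "All of the participants who meet the eligibility criteria will be included in the main analysis" and compares titres by study arm. None of these sections mentions samples taken after a third dose.

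**The concern.** The 6-month and 1-year GMTs are secondary outcomes of a trial that compares two two-dose regimens. If the third dose is taken up, the later 20 µg samples come from an unblinded, self-selected mixture of people with two and three doses, while the 30 µg samples still come from people with two. Section 7.2 gives raising immunity as the purpose of the extra dose, so the protocol itself expects it to move the quantity being measured.

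At stake is what the trial can say about the reduced dose over time, in the scenario where that dose has fallen short at four weeks. A by-arm comparison could then show a smaller deficit, or an advantage, that comes from the third dose. The 6-month cellular samples (20 participants per arm) are exposed in the same way.

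**Working it through.** The protocol gives no figure for this point to reproduce. Two things can be checked: the order of events, and how far a third dose could move the comparison.

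**1. Order of events**

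Inputs: doses are given "with a three week interval between both doses" (Vaccination); sampling times as above; planned start 3 May 2021 and planned end at the beginning of June 2022 (section 6.1); the trial ends with the last 1-year sample (End of the trial). The last dose 1 is therefore about 1 to 7 June 2021.

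- Primary sample: day 21 + 28 = 49 from dose 1.
- Each participant's own interval to the 6-month sample: 182 − 49 = 133 days; to the 1-year sample: 365 − 49 = 316 days.
- Last primary sample: 1 to 7 June 2021 + 49 days = 20 to 26 July 2021.
- First 6-month sample: 3 May 2021 + 182 days = 1 November 2021, which is 98 to 104 days (about 14 weeks) after the last primary sample.
- Last 6-month sample: 133 days (19 weeks) after the last primary sample.
- First 1-year sample: 3 May 2022, which is 281 to 287 days (over nine months) after the last primary sample.

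A third dose given within about 14 weeks of the last primary sample precedes every 6-month sample. Between about 14 and 19 weeks it precedes some of them. It precedes every 1-year sample unless it slips by more than nine months.

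**2. Effect on the comparison**

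Let d be the two-dose difference (20 µg minus 30 µg, log10), u the uptake in the 20 µg arm, and f the mean fold-rise among takers still present at sampling. The observed difference is D = d + u × log10(f), and the observed ratio is 10^D. The difference vanishes at f = 10^(−d/u).

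The value d = −0.15 is the non-inferiority margin (Sample size), a ratio of 10^(−0.15) = 0.71. The other d values, all u values and f = 3 (log10 = 0.477) are assumptions, as is the persistence of d to the late visit.

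| d (ratio) | u | D at f = 3 | Observed ratio | Break-even f |
|---|---|---|---|---|
| −0.15 (0.71) | 25% | −0.03 | 0.93 | 3.98 |
| −0.15 (0.71) | 50% | +0.09 | 1.23 | 2.00 |
| −0.15 (0.71) | 100% | +0.33 | 2.12 | 1.41 |
| −0.19 (0.65) | 25% | −0.07 | 0.85 | 5.75 |
| −0.19 (0.65) | 50% | +0.05 | 1.12 | 2.40 |
| −0.19 (0.65) | 100% | +0.29 | 1.94 | 1.55 |
| −0.30 (0.50) | 25% | −0.18 | 0.66 | 15.85 |
| −0.30 (0.50) | 50% | −0.06 | 0.87 | 3.98 |
| −0.30 (0.50) | 100% | +0.18 | 1.50 | 2.00 |

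The deficit shrinks in every row, and the sign changes in five of the nine.

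**3. How often the branch arises**

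This depends on what inferiority means, which the protocol does not settle. With SD 0.27 and the stated minimum of 50 per group, SE = 0.27 × √(2/50) = 0.054. At a true difference of 0, the chance of missing non-inferiority is 1 − Φ(0.15/0.054 − z): 21% for z = 1.960 (one-sided 2.5%) and 30% for z = 2.241 (one-sided 1.25%, the literal reading of a two-sided 2.5%). If inferiority instead means a confidence interval wholly below zero, the chance at a true difference of 0 is 2.5% or 1.25%. At a true difference of −0.15 it is 79% or 70%.

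**The case against.** The strongest reply is that handling samples after an extra dose is an intercurrent-event rule, which belongs in a statistical analysis plan that is not at hand. Section 3.2 lists GMTs at time points and does not mention persistence. Reporting by randomised arm, with the offered third dose as part of the strategy, is a legitimate summary. The sentence on including all eligible participants concerns the main analysis, not the late secondary GMTs. Much of this stands: the protocol fixes no wrong rule, and a by-arm summary is acceptable if labelled for what it is. However, a later plan can relabel samples but cannot supply a blood draw that was never taken. No sample is scheduled between four weeks after dose 2 and month 6, so a participant who takes the third dose in that interval has no two-dose value later than the primary sample.

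Stronger readings are tempting, and the protocol does not support them:

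- That any failed primary analysis triggers the offer. The stated trigger is inferiority. Blinding/unblinding treats the result as two-way, but does not say whether failing to show non-inferiority counts as inferiority.
- That the third dose certainly precedes the 6-month sample. Neither the analysis nor the offer is dated, and the Data analysis section warns that communication of results may be delayed by laboratory capacity.
- That the late comparison will reverse. At 25% uptake and a 3-fold rise it does not in any row of the table.
- That reactogenicity after the third dose goes uncollected. Sampling visits sends a questionnaire one week after each vaccination dose, wording that can cover a third.
- That restricting the late comparison to samples without a third dose restores a randomised comparison. Uptake is voluntary and unblinded, and at full uptake the 20 µg side would be empty.

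**Conclusion.** The point holds, confined to the inferiority branch. There, the third-dose provision and the unconditional late outcomes do not fit together. The 1-year comparison would practically certainly mix two-dose and three-dose 20 µg participants, provided anyone accepts the offer. The 6-month comparison would do so throughout if the dose is given within about 14 weeks of the last primary sample, and in part up to about 19 weeks. The direction of the distortion is clear: if the third dose raises titres, as intended, it favours the 20 µg arm. Its size is not, because uptake and fold-rise are assumptions; the results run from attenuation to reversal.

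The primary outcome, the dose-2 GMT and the 4-week neutralisation outcome are untouched. This is a worthwhile amendment to protect a secondary objective, not a threat to the main conclusion.

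**What to change.** Leave the third-dose offer as it is. Reconcile section 3.2, Sampling visits, Statistical analyses and Table 1 with Discontinuation criteria, Blinding/unblinding and section 7.2:

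- State that, in the inferiority branch, the by-arm 6-month and 1-year GMTs include an offered third dose and are not interpreted as persistence of the two-dose regimen. Apply the same statement to the 6-month cellular results.
- Record the date of any extra dose, if the eCRF does not already do so, and report samples taken after it separately, by number of doses received.
- Draw one 5 mL serum tube, of the type already used, just before the third dose. Use this last two-dose value in a supportive model of titre by time since dose 2.
- Label any comparison limited to samples without a third dose as supportive and non-randomised.

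Cost: protocol wording, at most one date field, and one tube per participant who takes the third dose. Limits: no 30 µg sample is scheduled at exactly the time of that tube, so the model must bridge between visits, and few 20 µg participants may remain without a third dose at the late visits.
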